#### 2.3.2. Exclusion Criteria

The data of those patients who have had to apply another therapy (pharmacological, surgical, or rehabilitative) during the care provided by the physiotherapist in their usual clinical practice will not be included. For ethical reasons, this will not be explicitly explained to the families who agree to participate in this study, so as not to influence possible therapeutic decisions in the following two months. Data of the children will be followed up and can be excluded later if there is a change in their diagnosis and cerebral palsy is not confirmed at the appropriate age. The previous therapeutic trajectory, as well as concomitant treatment (such as pharmacological treatment for spasticity, dystonia, epilepsy, etc., as well as other rehabilitation interventions) was not considered within the exclusion criteria for two reasons: their effect would already be included within the rate of motor development before VT, and also because all the children were compared only to themselves. These will be noted and considered during the calculations, but the data exclusion will only occur if there are changes in them (both adding or withdrawal) during our 2 months of intervention. 

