### 2.6. Sample Size Calculation and Statistical Analysis

Sample size calculation: The prevalence of cerebral palsy is 2.08 cases/1000 births. To obtain a good sample security, 30 subjects for each of the groups to be evaluated offer a confidence interval of 95% with a security of 10.

The initial GMFM and IMP score will be divided by the child’s months of age to calculate the rate of acquisition of their items so far. This calculation represents the mean distribution of the acquisition of these motor items. The acceleration values will be used to avoid errors in the assumption of how these items were acquired, since the tendency is to be exponential at these ages. The net values obtained in the valuation will not be considered, but the rate with which they have been obtained as a function of time will be. The rate of this development without intervention will be calculated at the time of the initial assessment, relative to the age of the patient. The proportion of the score necessary to obtain in the next two months to be able to accelerate that rate, instead of following the same previous trajectory, will be an unknown concept for all therapists and examiners.

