## 3. Methods and Timeline

Phase 1. Initial Assessment: Children who go to the rehabilitation center where they have been referred will be treated, an initial routine clinical examination will be performed, including: Personal/medical data collection.GMFM quantification.Treatment with the physiotherapist.Training of the parents in the home program.Recording for the IMP quantification.

Phase 2. Intervention period (2 months): The assignment to the therapist will be randomized according to the needs of the service, where each therapist will adapt the treatment according to the initial assessment. Both assessors and therapist cannot be blinded to the allocation or treatment, and both required live-direct performance. An external assessor (blind to both) will be able to score the IMP recordings. 

Children will receive weekly or fortnightly treatment, and their parents, family members, or carer will be trained in carrying out a home program. Each therapist will adapt the treatment according to the initial evaluation, as is usually performed in the rehabilitation service. During the treatment sessions, the physiotherapist will apply the therapy directly, either based on Vojta therapy or conventional physiotherapy. The frequency of repetition of the treatment at home and in the hospital will be recorded, depending on the availability of each family and the normal functioning of the service.

Phase 3. Second assessment at 2 months (±1 week, depending on follow up appointments).

Collection of data on the possible changes made in previous treatments and the frequency of home treatment (possible incidents due to illness or family limitations).GMFM quantification.Recording necessary for IMP quantification.

Children carried on clinically with the intervention, but this short period would allow us to attribute changes to RL, controlling better the influence of other factor (such as age maturation or other therapy inputs).

Study length. The data collection will be carried out for 4 years from the approval of the CEI. Only patients receiving healthcare with any of the therapies under investigation after authorization by the CEI will be included.

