### Statistical Methods

Statistical analysis will be performed using the SPSS 27.0 statistical software for Windows (SPSS Inc., Chicago, IL, USA; version 27.0). The normality of the sample will be checked using the Shapiro–Wilk test, and if it follows a normal distribution, an analysis of variance (ANOVA) of repeated measures p will be used, with time (pre-treatment and post-treatment) as an intra-group factor, and Vojta and conventional physiotherapy groups as the inter-group factor, all with a Bonferroni correction. Statistical analysis will be performed with a confidence level of 95%, so a *p*-value of <0.05 will be considered significant.

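### The protocol bases attribution on within-child change but fits a two-arm ANOVA, and never says that the Vojta-versus-conventional contrast decides; normal maturation can then be read as a Vojta effect

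*Protocol article*

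**What the plan says.** Section 2.1 describes two groups, Vojta therapy and conventional physiotherapy, with assessment before treatment and two months later. The Statistical Methods section plans a repeated-measures ANOVA "with time (pre-treatment and post-treatment) as an intra-group factor, and Vojta and conventional physiotherapy groups as the inter-group factor", "all with a Bonferroni correction", at the 5% level. It does not name time, group or their interaction as the test of the hypothesis.

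Other sections reason as if there were one arm:

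- Section 2.3.2 gives two reasons for not excluding children on prior or stable concomitant therapy. One is that its effect is already contained in the rate of development before Vojta therapy. The other is that "all the children were compared only to themselves".
- Section 3 explains the two-month window by saying that "this short period would allow us to attribute changes to RL" (RL being reflex locomotion), with better control of influences such as maturation.
- The hypothesis (1.1) and main goal (1.2) speak of improvement or change with Vojta therapy and name no comparator. Among the goals, a contrast with children not treated by Vojta appears only in a secondary, long-term one (1.3).

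Section 2.6 says acquisition tends to be exponential at these ages, and that rates rather than net scores will be used. Section 4 adds a check against the highest possible pre-intervention rate, which places all earlier items in the last two months before treatment.

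**The concern.** The two descriptions answer different questions. Comparing a child with itself measures maturation plus whatever treatment adds. Comparing the arms removes the maturation that they share. A short window reduces maturation but does not separate it from treatment, and at 0 to 36 months two months of development is not negligible.

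The same fitted ANOVA could therefore support opposite conclusions. A significant time effect, or a significant change in the Vojta arm, would fit the attribution sentence in section 3 and could be taken as confirming the hypothesis even if both arms gained equally. Section 4 would draw far-reaching conclusions about mechanism from a confirmed hypothesis, so the choice of term matters.

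**Working it through.** **Inputs from the protocol.** 30 children per arm (2.6); two assessments, 2 months apart (3); significance at 0.05 (Statistical Methods), taken as two-sided; ages 0 to 36 months (2.3.1); allocation by therapist availability (2.1, 2.3). The protocol gives no effect size, SD, pre/post correlation or expected 2-month gain, so there is no figure of its own to reproduce on this point.

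**Assumptions.** Pre/post correlation r = 0.7; maturation common to both arms of 0.3, 0.5 or 0.8 baseline SD; no difference between Vojta and conventional care.

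**Step 1: what each term tests.** The SD of a child's change is √(2(1 − r)) = √0.6 = 0.775 SD.

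- Time effect, 60 children: standard error 0.775/√60 = 0.10. Maturation of 0.3 SD lies 0.3/0.10 = 3.0 standard errors from zero.
- Change within the Vojta arm, 30 children: standard error 0.775/√30 = 0.141, so 0.3 SD lies 0.3/0.141 = 2.1 standard errors from zero.
- Group × time: the difference between the two mean changes. Common maturation cancels and the expected value is zero.

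Share of 4,000 simulated trials with p < 0.05 and no treatment difference (Monte Carlo standard error near 5%: √(0.05 × 0.95/4000) = 0.3 percentage points):

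| Maturation (SD) | Time effect | Change within Vojta arm | Group × time | ANCOVA on baseline |
|---|---|---|---|---|
| 0.3 | 85% | 54% | 4.8% | 5.0% |
| 0.5 | 99.9% | 93% | 5.2% | 5.2% |
| 0.8 | 100% | 100% | 4.7% | 5.6% |

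The group main effect is no substitute, because it averages the baseline into the contrast. With a 0.5 SD baseline difference between arms and no treatment effect, it was significant in 43% to 56% of trials.

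**Step 2: does the rate scale remove the problem?** Assume score ∝ age^k with no treatment effect. At age a months the post/pre rate ratio is [((a+2)^k − a^k)/2] ÷ [a^k/a]. For a = 12 and k = 1.5 this is [(52.38 − 41.57)/2] ÷ [41.57/12] = 5.41/3.46 = 1.56. Over ages 6 to 24 months:

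| k | Ratio to average pre-rate |
|---|---|
| 1.0 | 1.0 |
| 1.3 | 1.3–1.4 |
| 1.5 | 1.5–1.6 |
| 2.0 | 2.1–2.3 |

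Whenever growth accelerates, as section 2.6 expects, the rate rises without any treatment effect.

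**Step 3: does the maximal pre-rate check in section 4 remove it?** The denominator becomes a^k/2. For a = 12 and k = 1.5 the ratio is 5.41/20.78 = 0.26. Over k = 1 to 2 and ages 6 to 24 months it runs from 0.08 to 0.78. This check over-corrects, while the ordinary rate under-corrects when growth accelerates. Both are within-child comparisons and neither isolates treatment.

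**Step 4: is a different model needed?** The detectable difference with 30 per arm and 80% power is √(2/30) × (1.96 + 0.84) × f = 0.723 × f, in baseline SD. Here f = √(2(1 − r)) for group × time and √(1 − r²) for ANCOVA.

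| r | Group × time | ANCOVA |
|---|---|---|
| 0.3 | 0.86 | 0.69 |
| 0.5 | 0.72 | 0.63 |
| 0.7 | 0.56 | 0.52 |
| 0.9 | 0.32 | 0.32 |

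ANCOVA adds precision, but little when the correlation is high. Nor is either model safe in all cases when allocation is not random. With a stable 0.5 SD baseline difference and parallel trends, ANCOVA is biased by +0.16 SD (12.4% false positives) and group × time is not (5.4%). If instead there is no effect conditional on baseline, group × time is biased by −0.15 SD (11.4%) and ANCOVA is not (5.2%).

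**Step 5: why age belongs in the model.** With a 6-month difference in mean age, no effect, and an illustrative raw-score curve (score ∝ age^0.6, 3,000 runs), false positives were 12.2% for group × time, 12.7% for ANCOVA on baseline alone, and 5.1% for ANCOVA on baseline and age. GMFCS was not simulated.

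**The case against.** The strongest reply is that the term that decides, the covariates and the scope of Bonferroni are details for an analysis plan, which is not shown, and that a time-by-group ANOVA with two groups is normally read through its interaction. That stands as far as silence goes. It does not cover sections 2.3.2 and 3, which state a basis for attribution that conflicts with the model.

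The protocol also does not ignore the issue. Section 4 discusses natural acceleration and adds the maximal pre-rate check. Section 2.3.2 says other therapies will be noted and taken into account, and excludes children whose therapy changes during the two months. These are real safeguards, but they are still comparisons of a child with itself.

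A reader might infer several stronger points that the documents do not support:

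- *That the ANOVA must be replaced by ANCOVA.* Common maturation already cancels in group × time. ANCOVA on the 2-month raw score would also use the net values that section 2.6 sets aside.
- *That group × time has a badly inflated error here.* The inflated figures come from raw scores under an assumed age imbalance.
- *That the arms do differ in age, severity or prior therapy.* Allocation by therapist availability means only that they may.
- *That the Bonferroni correction does nothing.* It would be empty across two-level factors, but it may be meant to cover GMFM and IMP.

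**Conclusion.** The point holds as a contradiction within the protocol. Sections 2.3.2 and 3 draw the conclusion from within-child change, the Statistical Methods section fits a two-arm model, and nothing says that the between-group term decides. If the time effect or the within-Vojta change were taken as the test, maturation alone would give a positive result in 54% to 100% of trials, against about 5% for group × time. These figures rest on assumed maturation of 0.3 to 0.8 SD, correlation 0.7 and comparable arms. The direction needs only that children gain over two months in both arms, or, on the rate scale, that acquisition accelerates as section 2.6 says.

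The planned model is not shown to be wrong. It contains a usable test once that test is named. Neither group × time nor ANCOVA guarantees an unbiased contrast when allocation follows therapist availability.

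**What to change.** - State that the sole test of the hypothesis is the Vojta-versus-conventional difference over the 2 months, that is, the group × time term or equivalently the difference in mean change, with a 95% confidence interval.
- Name one outcome scale for that test, consistent with sections 2.6 and 4, which set aside net scores and comparisons of absolute GMFM values between children.
- Adjust for age and GMFCS level, both already listed in section 2.5.
- Allow baseline-adjusted ANCOVA as an alternative or sensitivity analysis, and say that neither model guarantees an unbiased contrast under this allocation.
- Label within-group changes, including the maximal pre-rate comparison, as descriptive.
- Delete or correct the self-comparison sentence in section 2.3.2 and the attribution sentence in section 3.

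The cost is wording and a few degrees of freedom out of 60 children, with no new data to collect. Section 4 reports complete data for only four children, so the test can still be fixed before results are known.

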## 4. Discussion and Ethical–Legal Aspects

Completed assessment data of four subjects has been collected to date, as two subjects withdrew prematurely or did not sign the consent form. Recruitment is currently ongoing at our first site and no results report is available due to the small sample. 

The baseline scoring of GMFM at initial assessment is related to the age of the child in order to understand the rate of items acquisition so far. The aim of this study is not to compare absolute values of GMFM between different subjects according to their age and, therefore, if the children are born preterm, the chronological age is considered. This allows us to plot changes due to spontaneous and therapeutic gross motor experience after birth. 

The rate values are calculated by dividing the total score by the time (days of age) required to achieve it, assuming that the neonatal GMFM would be zero. The acceleration factor is calculated by dividing the differences between final and initial rate (assumed to be zero at birth), by the age in days (elapsed time). The same rate and acceleration factors of acquisition are figured out between the initial assessment and after two months of the intervention. Only new points acquired during this period were considered to calculate the rate of development and acceleration values in the intervention period. Because the distribution of the item acquisition during the pre-intervention period is unknown, we performed a second rate calculation assuming that all the items were adquired during the last two months before the intervention (for children older than 2 months at initial assessment). This simulation of the maximal possible pre-intervention rate and acceleration will limit the possibility of being overcome by the post-treatment values and will avoid average values slowing down the last two preintervention months. Completing all the items in the previous two months is unlikely and would make it more difficult to obtain improvements after the intervention, especially for the older children. Even if these calculations do not benefit our results, they will ensure that the rate and acceleration post-intervention can be compared within same-lasting and following periods. We know that the GMFM item acquisition is not linear, and both calculations will help us to understand if the rate differences are due to natural acceleration or a significant therapeutic change. On the other hand, this will avoid comparing low average rate values due to longer pre-intervention periods and, therefore, random positive outcomes. Rate values within each GMFM dimension will then be considered and will help to clarify the results. 

If our hypothesis is confirmed, it would imply that gross motor function (including postural control and righting at every developmental milestone) has to be onset regardless of training and experience. Therefore, this bodily function is automatic and develops through postural ontogenesis in the first year of life. Vojta therapy would be the key to unlocking the development of gross motor function, later used in the movement of daily life activities, including other therapies, such as conventional physiotherapy, sensory stimulation, occupational therapy, etc. Data of their previous therapy inputs (physiotherapy, occupational therapy, hydrotherapy, surgery, botulin toxin) were also included, as well as Gross Motor Function Classification System (GMFCS), age, type of cerebral palsy, locomotion stadium, 21 daily doses of treatment at home, and frequency of follow ups and treatment of the therapist. The influence of these factors in our results will make us understand which interventions can have a complementary effect, as well as pointing towards the therapeutic mechanisms of VT. 

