## Abstract

Background: Infantile cerebral palsy is a neurological pathology that causes great morbidity, mortality, and disability in people who suffer from it, mainly affecting motor development. There are a multitude of non-pharmacological methods or therapies for its treatment. One of the main methods is Vojta therapy. This methodology acts on ontogenetic postural function and automatic postural control. Objective: This study aims to demonstrate that there are changes in the motor development of children with cerebral palsy with the application of Vojta therapy. Methods and analysis: This is a randomized controlled trial on the effectiveness of two neurorehabilitation techniques in patients with cerebral palsy conducted at the Physical Medicine and Rehabilitation Service of the Teresa Herrera Maternal and Child Hospital of the A Coruña and Cee Health Area. The study will be conducted from January 2023 to December 2024. There will be two groups: the Vojta therapy group (*n* = 30) and the conventional physiotherapy group (*n* = 30). The measurement variables will be gross motor function as measured by the Gross Motor Function Measure (GMFM) and Infant Motor Profile (IMP) scales. Ethics and dissemination: The study was approved by the Research Ethics Committee of the University of Murcia (1823/2018) and Comité de Ética de la Investigación de A Coruña-Ferrol (2022/099). Trial registration number: ClinicalTrials.gov; identifier: NCT06092619.

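### The stated pre/post ANOVA compares change scores only among children seen at both visits, which is biased if loss or exclusion depends on baseline differently by arm and less precise than adjusting for baseline

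*Protocol article*

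**What the plan says.** - **Analysis.** Under Statistical Methods, if normality holds, "an analysis of variance (ANOVA) of repeated measures p will be used, with time (pre-treatment and post-treatment) as an intra-group factor" and treatment group as the between-group factor.
- **Visits.** Section 3 has one post-baseline visit: "Second assessment at 2 months (±1 week, depending on follow up appointments". Section 4 computes the intervention-period rate and acceleration from the points gained between the initial assessment and that visit.
- **Exclusions after entry.** Section 2.3.2 drops a child's data if a concomitant treatment is added or withdrawn during the 2 months, and also if cerebral palsy is later not confirmed.
- **Loss so far.** Section 4: "Completed assessment data of four subjects has been collected to date, as two subjects withdrew prematurely or did not sign the consent form". Section 2.3.1 makes signed consent a condition of inclusion.
- **Sample size.** Section 2.6: "30 subjects for each of the groups to be evaluated offer a confidence interval of 95% with a security of 10". It has no term for loss and does not say whether the 30 are enrolled or completed.
- **Allocation.** Sections 2.1 and 2.3 assign children by therapist availability and call the design pseudo-randomized.

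**The concern.** With two time points, the group-by-time test of this ANOVA is the same test as a comparison of mean change between arms. It uses complete pairs only. A child without the 2-month assessment adds nothing, and the treatment-change rule removes further children for something that happens after assignment.

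The analysed children are therefore selected after entry. If that selection is related to baseline function and differs between the arms, the completers no longer share a baseline distribution, and mean change can differ with no treatment effect. Different loss is plausible but not shown. Section 2.7 recommends a Vojta home dose of four times a day and states no frequency for the control arm, and treatment changes may follow a child's progress.

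There is also a cost without any loss. The baseline is measured on every child, yet a change score uses it less efficiently than a model that adjusts for it.

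**Working it through.** **1. The plan's figure.** Section 2.6 gives 30 per group. Taking its security of 10 as a half-width d = 0.10 (an assumption), n = z²p(1−p)/d² with z = 1.96:
- p = 0.00208: 3.8415 × 0.00208 × 0.99792 / 0.01 = 0.80, so 1 child.
- p = 0.5: 3.8415 × 0.25 / 0.01 = 96.04, so 97.

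Neither gives 30, and the sentence has no loss term. The derivation therefore cannot show whether 30 is enrolled or evaluated.

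**2. Early loss.** Four children completed and two were lost. Only consented children are participants, so post-entry loss is 2 of 6 (33%) if both withdrew, 1 of 5 (20%) if one did, and 0 of 4 if neither had consented. The exact 95% interval for 2 of 6 is 4% to 78%. No rate can be projected.

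**3. Precision with no loss.** Assumptions: equal pre and post SD of 1, correlation ρ = 0.6, n = 30 per arm.
- Change score: SE = √[(2/n) × 2(1−ρ)] = √(0.0667 × 0.80) = 0.231 SD.
- Baseline-adjusted: SE ≈ √[(2/n) × (1−ρ²)] = √(0.0667 × 0.64) = 0.207 SD.
- Ratio: √[(1+ρ)/2] = 0.894, about 10% smaller. At ρ = 0.8 it is √0.90 = 0.949, about 5% smaller.

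**4. Bias with unequal loss.** Simulation with no true effect, 30 per arm, ρ = 0.6 and 4,000 trials per setting. About 33% to 38% are lost in one arm, more often at lower baseline (logit slope as shown), and about 10% in the other. All of these inputs are assumptions.

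| Logit slope | Change-score bias (SE) | Baseline-adjusted bias (SE) | SE reduction |
|---|---|---|---|
| 0.5 | −0.061 (0.265) | 0.000 (0.240) | 9% |
| 1.0 | −0.119 (0.264) | 0.002 (0.244) | 8% |
| 1.5 | −0.159 (0.267) | −0.002 (0.248) | 7% |

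The largest bias is 0.159/0.267 = 0.6 of its standard error. Over these settings the change-score test rejects a true null about 6% to 9% of the time instead of 5%.

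**5. Cross-check.** With equal SDs, expected change falls by (1−ρ) per unit of baseline, so bias = −(1−ρ) × (difference in completers' mean baseline). At ρ = 0.6 the biases above correspond to baseline differences of 0.061/0.4 = 0.15, 0.119/0.4 = 0.30 and 0.159/0.4 = 0.40 SD. For a difference of 0.30, ρ = 0.4 gives −0.18 and ρ = 0.8 gives −0.06.

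**6. When there is no bias.** If baseline-related loss is the same in both arms, the completers' baselines shift equally and the bias is 0.00, which simulation confirms.

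**7. Limit of the model.** These are generic standardised scores, whereas the trial analyses rates and accelerations. If the post-treatment SD exceeds the baseline SD, the slope of change on baseline, ρ × (SD post / SD pre) − 1, moves towards zero (at ρ = 0.6 it reaches zero when the ratio is 1/0.6 = 1.67) and can change sign. The bias then shrinks or reverses.

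**The case against.** Three stronger readings are tempting, and the article supports none of them.

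- **A third of the children are being lost, so 30 per group becomes 20.** The two lost children mix withdrawal with missing consent, and a child without consent was never a participant. The planned 30 may also mean completers: recruitment is ongoing, further sites may join, and Section 3 gives 4 years of data collection.
- **A child who stops therapy cannot be scored.** No section says so. Section 3 schedules the second assessment and records interruptions to home treatment, and Section 2.7 keeps low-frequency families as a dose category. Only a child who misses the 2-month assessment, or is excluded, is lost.
- **The change contrast is valid only if loss is unrelated to baseline.** Equal baseline-related loss in both arms leaves it unbiased. In the simulated case, where low-baseline children leave one arm, the error goes against that arm. If that is the Vojta arm, the error works against the trial's hypothesis.

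It can also be said that no arm-specific loss is reported, that parents in both arms are trained in a home programme, and that missing-data handling and loss allowances commonly sit in a full protocol or SAP not shown here. All of that stands. It does not reach the two things the article does fix: a change-score test on complete pairs, and an exclusion triggered by events after assignment. Thirty completers per arm can still be a selected thirty.

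**Conclusion.** The point holds in a limited form. The named analysis compares change among children with both visits, after a post-entry exclusion, and a better use of data already collected is available.

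The bias is conditional. It is about 0.06 to 0.16 SD if roughly 35% of one arm, weighted to low baseline, and 10% of the other are missing and the correlation is 0.6. It is nil if loss is alike in both arms, and it can take either sign. The precision cost does not need any loss: the standard error is about 10% larger than necessary divided the other way, 0.231 against 0.207 SD, at correlation 0.6 with equal SDs.

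The loss rates, baseline dependence and correlation are assumptions, since the article gives none of them. The early count shows that loss may occur, not how often. This is worth changing while few children have been assessed, but it does not by itself undermine the trial.

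**What to change.** 1. **Follow-up.** Seek the 2-month GMFM and IMP recording for every consented child, including those who stopped or changed therapy, unless the parents withdraw consent to use of the data.
2. **Analysis set.** Keep all these children in the main analysis. Make the treatment-change exclusion of Section 2.3.2 a sensitivity analysis.
3. **Model.** Replace the change-score ANOVA by ANCOVA of the 2-month outcome on group, baseline score and age. The intervention-period rate can stay as the outcome: with a near-constant 2-month interval it is the gain rescaled, and with baseline score in the model the group comparison is essentially the same. SPSS MIXED with both visits as outcomes is an alternative that uses children with a baseline only, but with no loss it returns the change-score contrast and so brings no gain in precision. Do not force equal baseline means, because allocation is by therapist availability.
4. **Sensitivity.** Add one analysis that gives children without a 2-month assessment a poorer outcome.
5. **Reporting.** State whether 30 per group means enrolled or evaluated. Report non-consent, withdrawal and Section 2.3.2 exclusions separately, by arm.

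The cost is slightly more analysis and follow-up contact. Baseline adjustment does not remove bias if the arms truly differ at baseline, which this allocation allows.

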### 2.3. Participants

Participant selection allows the randomization of the sample following the natural ordering of the rehabilitation service where the study is carried out. The assignment of children to their different therapists is performed according to the available treatment times of the latter. In other words, patients are assigned to one treatment or another following criteria of immediacy as part of the regular routine of the rehabilitation service. Therefore, the randomization will be carried out through the needs of the service, as is already the case.

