#### 2.3.1. Inclusion Criteria

Male and female children between 0 and 36 months, with a risk of neurological alteration or diagnosis of cerebral palsy or neuromotor disease, who are admitted for assessment and/or treatment according to the Vojta therapy methodology or conventional treatment in the Physical and Rehabilitation Medicine Service will be included in this study. The diagnosis may be clinical and/or supported by the presence of lesions in complementary tests. Due to the fact that the diagnosis of cerebral palsy is confirmed in many cases after one year of life, the data of children in treatment for risk of neurological alteration will only be included retrospectively when said diagnosis has been confirmed. Younger children have not received a definite diagnosis of CP yet, but, based on the presence of lesions determined by magnetic resonance imaging, their risk of developing CP was estimated to be sufficiently high to justify their inclusion in the CP group. 

Parents or guardians must sign the informed consent that will allow us to use their data on therapeutic results, always in a pseudonymized (coded) way, guaranteeing confidentiality. 

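### Inclusion and exclusion of children's data are settled after a known, unconcealed allocation, so who is analysed in each arm can depend on events after allocation

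*Protocol article*

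**What the plan says.** All references are to the protocol article.

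- **Allocation.** Section 2.3 says that "patients are assigned to one treatment or another following criteria of immediacy as part of the regular routine", meaning by which therapist has time free. Section 3, Phase 2, says "The assignment to the therapist will be randomized according to the needs of the service". Sections 2.1 and 3 state that therapists and GMFM assessors cannot be blinded; only the external scorer of the IMP videos is.
- **Entry.** Section 2.3.1 says "the data of children in treatment for risk of neurological alteration will only be included retrospectively", that is, once the diagnosis is confirmed, which in many cases happens after the first birthday. The next sentence says that younger children without a definite diagnosis were placed in the cerebral palsy group because of MRI lesions.
- **Removal.** Section 2.3.2 allows a child to be excluded later if cerebral palsy is not confirmed. It also excludes data if a concomitant treatment is added or withdrawn during the two months.
- **Consent.** Section 2.3.1 requires it: "Parents or guardians must sign the informed consent that will allow us to use their data on therapeutic results". No time point is given. On the co-treatment exclusion, section 2.3.2 says "this will not be explicitly explained to the families who agree to participate in this study". The reason that it gives for withholding the rule is "so as not to influence possible therapeutic decisions in the following two months". Section 4 reports "Completed assessment data of four subjects has been collected to date" and that "two subjects withdrew prematurely or did not sign the consent form".
- **Schedule.** In section 3, Phase 1 lists data collection, GMFM, treatment, parent training and the IMP recording. Assignment to the therapist appears under Phase 2. Consent appears in no phase.

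**The concern.** A comparison of two arms is protected only if the set of children analysed is fixed before allocation, or by events that allocation cannot influence. Here three events settle who is analysed, and all can occur after the arm is known: confirmation of the diagnosis, non-confirmation, and a change of co-treatment. Each can plausibly be linked to how the child is progressing. A child who progresses well may be less likely to have cerebral palsy confirmed, which would remove good responders. A child who progresses poorly may be more likely to have a treatment added, which would remove poor responders. These links are inferences; the article does not state them. If either acts more strongly in one arm, the arms differ through selection even when the therapies are equivalent. Because it arises after allocation, better random sequence generation alone would not prevent it.

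**Working it through.** The plan gives no figure to reproduce on this point. The check is a reading of the sections together, followed by an illustration of size.

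**1. Can the outcome be known before inclusion is decided?** The intervention period is 2 months (section 3). Section 2.3.1 puts confirmation after one year of age in many cases. A child starting before about 12 − 2 = 10 months of age then has the second assessment done before confirmation. Eligibility runs from 0 to 36 months, so such children are within scope.

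**2. Are the two entry rules compatible?** One sentence includes at-risk children's data only after confirmation; the next includes younger children on MRI risk without it. For an unconfirmed infant with MRI lesions, the first says not yet and the second says yes. They must be reconciled.

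**3. Is allocation known when these decisions are made?** Yes, to therapists and GMFM assessors (sections 2.1 and 3). Allocation by availability is part of routine scheduling, and no concealment step is described.

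**4. Is the order of steps fixed?** No. Treatment and parent training stand in Phase 1 and assignment in Phase 2, although a child must have a therapist before being treated. Nothing places consent before assignment.

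**5. How large could the bias be?** Assume no true effect, gains with SD 1, 30 analysed per arm (section 2.6), a two-sided t-test at 0.05, and a share q of the lowest gainers missing from one arm only. The expected bias is φ(z_q)/(1 − q). For q = 0.10: z = −1.282, φ = 0.1755, and 0.1755/0.90 = 0.195 SD. A simulation with 20,000 repetitions gave:

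| Lost from one arm | Bias (SD) | Type I error |
|---|---|---|
| lowest 5%, all lost | 0.11 | 7% |
| lowest 10%, all lost | 0.20 | 12% |
| lowest 20%, all lost | 0.35 | 32% |
| lowest third, all lost | 0.55 | 69% |
| lowest 20%, half of them lost (10% overall) | 0.16 | 10% |

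Losing the highest gainers gives the same sizes with the opposite sign. The arm, the share lost and its link to gain are all assumed.

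**The case against.** **Consent.** A reader might infer that consent is taken after the child has been assigned and treated, or even after the two-month result. The documents do not support that. No section gives the timing. The section 4 remark joins two reasons with an *or*, and it equally fits families who declined at first contact. Section 2.3.2 points the other way: it speaks of families who agree while the two months still lie ahead, so agreement comes at or near the start. It does not, however, place consent before the therapist is known. As a condensed article may leave the consent step to the full protocol, its absence from section 3 is no error in itself.

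**Phase 1.** The list is unnumbered and may not be meant as a strict order. That is fair, and it limits this part to a need for clarification. Assignment nevertheless sits in a later phase than treatment.

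**Retrospective inclusion.** The sentence concerns data, and section 2.3.2's wording on follow-up and later exclusion fits prospective entry with later confirmation. This reading is reasonable, but the analysed set is still settled by later confirmation.

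**Own-control comparison.** Section 2.3.2 says that children are compared only with themselves. The Statistical Methods section nevertheless includes group as a between-subject factor, and selection on the change itself is not removed by subtracting a baseline.

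**Diagnosis.** Restricting the target population to confirmed cerebral palsy is a legitimate interest, and confirmation resting on imaging alone would be hard for treatment to influence. But section 2.3.1 allows a clinical diagnosis.

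**Loss and burden.** If the two lost children are additional to the four completed, 2/6 = 33%. The exact 95% interval is about 4% to 78%, arms are pooled and reasons are mixed, so this says nothing about differential loss. Nor do the documents show that the home programmes differ in demand: section 2.7 gives a home frequency for Vojta only.

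**Conclusion.** The point holds on stated text. Retrospective inclusion on confirmation, later exclusion for diagnosis or co-treatment change, and an allocation known to staff together let entry to the analysis depend on events after allocation. That permits selection bias in either direction. The two inclusion rules in section 2.3.1 contradict each other, and section 3 needs its order of assignment and treatment made clear.

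That bias has occurred, that consent is late, or that loss differs by arm is not shown. The size is therefore illustrative: about 0.1 to 0.35 SD, with a type I error of 7% to 32%, if the lowest 5% to 20% of gainers were lost from one arm only. Blinded IMP scoring guards against measurement bias but not against this. With four children complete out of a planned 2 × 30 = 60, the rules can still be changed for most of the sample.

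**What to change.** 1. Reconcile the two inclusion rules in section 2.3.1 by registering every eligible child prospectively, at-risk infants included.
2. Re-order Phase 1: eligibility and signed consent; baseline GMFM and IMP recording; assignment and disclosure of the therapist; first treatment and parent training. Move assignment out of Phase 2.
3. Make the main analysis all registered children in their assigned arm. Use the subset with confirmed diagnosis and unchanged co-treatment as a sensitivity analysis, so that the section 2.3.2 exclusions no longer determine the main result.
4. Report refusals, withdrawals and later exclusions separately, by arm where a child has been assigned.

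**Cost.** A protocol amendment and a re-ordered first appointment, with no extra staff or procedure. Two small downsides remain: a few families may decline when asked before the therapist is known, and the main analysis will include some children whose diagnosis is not later confirmed.
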